## Abstract

Gastroesophageal reflux disease (GERD) is a common chronic condition mainly caused by the dysfunction of the antireflux mechanism at the gastroesophageal junction. This is composed of the lower esophageal sphincter and the crural diaphragm. Increasing evidence suggests that diaphragmatic dysfunction and reduced inspiratory muscle strength may contribute to the persistence of GERD symptoms. Although respiratory physiotherapy has shown beneficial effects, the role of a structured inspiratory muscle training (IMT) program has not been sufficiently examined. This study aims to investigate the effects of an inspiratory muscle training program on inspiratory muscle strength and secondary clinical outcomes in individuals with GERD. A total of thirty adults with a confirmed GERD diagnosis will be enrolled in a two-arm randomized controlled trial. These volunteers will be randomly assigned either to the experimental group, which will undergo a 3-month inspiratory muscle training (IMT) using tapered flow resistive loading at 40% of maximal inspiratory pressure (MIP), or to the control group, which will receive sham IMT with a consistent low resistance. Primary outcomes will include maximal inspiratory pressure (MIP) and maximal dynamic inspiratory pressure (S-index). Secondary outcomes will assess GERD symptoms, disease-related quality of life, and pulmonary function. Measurements will be performed at baseline, at three months of intervention, and at six months from recruitment (follow-up). IMT is expected to lead to significant improvements in inspiratory muscle strength, symptom burden, and quality of life compared with sham training. This trial will provide novel evidence regarding the role of inspiratory muscle training as a non-pharmacological intervention in the management of GERD. **Trial registration:** ClinicalTrials.gov Identifier: NCT07131397.

## 1. Introduction

Gastroesophageal reflux disease (GERD) is a chronic condition of the upper gastrointestinal tract, characterized by the repeated backward flow of stomach contents into the esophagus, leading to esophageal symptoms such as heartburn, as well as extraesophageal ones like chronic cough and wheezing. The persistence of these symptoms is consistent with an impaired antireflux barrier [1].

The antireflux barrier is a functional unit consisting of the intrinsic lower esophageal sphincter (LES) and the diaphragmatic sphincter [2]. During normal processes such as swallowing, a coordinated relaxation of both components allows the passage of the bolus into the stomach [3,4]. This is followed by a rapid restoration of the barrier pressure, which is higher than the intra-abdominal pressure, preventing the reflux of gastric contents. Transient lower esophageal sphincter relaxations represent another important contributor to reflux events. Although this phenomenon is physiological, its increased frequency and prolonged duration in individuals with GERD result in repeated inhibition of diaphragmatic activity, thereby weakening the extrinsic component of the antireflux barrier [3].

In GERD, the coordinated activation of the sphincters is often disrupted, leading to increased LES and femoral septum distensibility, thus reducing resistance to reflux episodes [3,4]. These episodes allow hydrochloric acid, one of the most toxic components of gastric juice, to cause inflammation in the esophageal epithelium, leading to severe esophageal mucosal damage [5]. Abnormal changes in intrathoracic and intra-abdominal pressures that alter diaphragmatic movement and contractility may be harmful [6,7,8].

Increasing evidence suggests that GERD is not limited to the gastrointestinal tract but is also associated with respiratory deficiencies. Individuals with GERD, even in the absence of diagnosed pulmonary disease, have been reported to exhibit reduced inspiratory muscle strength, altered airflow dynamics, and obstructive or restrictive airway pathology [9,10,11]. Proposed mechanisms include microaspiration of gastric contents and reflex bronchoconstriction mediated via the pneumovagal tract [12]. These respiratory manifestations contribute significantly to symptom burden and reduced quality of life [13].

Non-pharmacological interventions targeting the physiological mechanism of the antireflux barrier, especially those that have been widely implemented in respiratory disorders, have therefore gained increasing attention [14]. Respiratory physiotherapy and specific interventions targeting the enhancement of diaphragmatic function have been found to alleviate reflux symptoms and improve patient-reported outcomes [15]. Additionally, inspiratory muscle training (IMT) represents a focused strategy to strengthen the diaphragm through externally imposed specific load related to the individual’s maximal inspiratory pressure [16,17]. This is an individualized intervention with preliminary studies suggesting that it could augment gastroesophageal junction competence and reduce symptom severity. Thus, medication and the possibility of surgery might be reduced [18]. However, evidence remains limited by heterogeneous methodologies and trials with small sample sizes [16].

The present randomized controlled trial protocol is designed to address these gaps by systematically evaluating the effects of a structured IMT program on inspiratory muscle strength and disease-specific patient-reported outcomes in people with GERD. This study aims to clarify the role of diaphragmatic strengthening as a non-pharmacological management of GERD.

## 2. Objectives

The main aim of this randomized controlled trial is to assess whether a structured inspiratory muscle training intervention enhances inspiratory muscle strength, assessed through maximal inspiratory pressure and maximal dynamic inspiratory pressure, in patients with gastroesophageal reflux disease. Secondary objectives include evaluating changes in GERD symptom severity, disease-related quality of life, and pulmonary function following the intervention.

## 3. Methods

### 3.1. Study Design

This study is structured as a two-arm, parallel-group randomized controlled trial, conducted in line with the CONSORT guidelines and the SPIRIT recommendations for interventional trial protocols [19]. The study’s design is presented in Figure 1. The protocol has been prospectively registered on ClinicalTrials.gov (NCT07131397).

### 3.2. Study Setting

The trial will be coordinated by the Laboratory of Advanced Physiotherapy, Department of Physiotherapy, University of West Attica. Participant recruitment, delivery of interventions, and outcome assessments will take place at a private physiotherapy clinic located in Athens, Greece.

### 3.3. Recruitment Procedures

Participants will be recruited via social media invitations, providing a medical diagnosis of GERD and spirometry by a gastroenterologist and pulmonologist, respectively.

Diagnosis of GERD should be in accordance with the Lyon consensus criteria [20]. Measurement of the spirometry and the S index and the following information will be explained to the participants: (a) objectives, methods and clinical significance of the study, (b) the right to withdraw from the study at any time, (c) the voluntary nature of their participation, (d) information about the results of their assessments and (e) that their choice to take part in the study will not influence the delivery of research-related services, and failure to attend more than two scheduled treatment sessions or any deterioration in GERD symptoms will result in withdrawal from the study. All participants will be required to provide written informed consent, signed by the participant, the principal investigator, and two witnesses. This consent will authorize participation in the study and the publication of results, while allowing participants the right to withdraw at any point.

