### 3.4. Randomization and Blinding Procedures

The allocation concealment will be ensured through the randomization process. Sealed, opaque envelopes will be used, numbered consecutively by an Assistant Professor of the Laboratory of Advanced Physiotherapy, University of West Attica, who will not participate in any other process of the study. Participant assignment will be concealed from both participants and evaluators, while the principal investigator will be informed, in accordance with a single-blinding procedure.

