### 3.6. Outcome Measurements

The outcome assessments have been selected to capture both physiological changes in inspiratory muscle performance as well as clinically significant effects on the severity and frequency of GERD symptoms. A trained physiotherapist will perform: (a) MIP (Micro RPM), according to ERS statement [25,26], (b) S-index measurement (Powerbreathe K5) [27,28] and will administer the Reflux Disease Questionnaire [29,30,31] and Reflux-Qual Short Form Questionnaire [32,33]. All measurements will be performed in random order.

Respiratory function will be assessed with the measurement of FEV1/FVC% using the Spirolab iii spirometer (Medical International Research, Inc., Rome, Italy). This will be performed by a pulmonologist with adequate training.

All measurements will be performed at three pre-specified time points: at baseline (T1), immediately after completion of the 12-week intervention (T2), and at the six-month follow-up (T3) (Table 1).

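### The plan randomises the order of all measurements and promises participants their results without saying when, so a strength result could be known before the symptom and quality-of-life questionnaires are answered

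*Protocol article*

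**What the plan says.** Three parts of the protocol article bear on this.

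- **Section 3.3 (Recruitment Procedures).** The list of what is explained to participants opens with "Measurement of the spirometry and the S index and the following information will be explained to the participants" and has as one item "information about the results of their assessments". It does not name the results meant, and it does not say whether they are given at each visit or at the end.
- **Section 3.6 (Outcome Measurements).** A single trained physiotherapist performs MIP and S-index "and will administer the Reflux Disease Questionnaire" as well as the Reflux-Qual Short Form. The next sentence is "All measurements will be performed in random order". Later in the same section: "All measurements will be performed at three pre-specified time points", namely T1, T2 and T3.
- **Section 3.4 (Randomization and Blinding Procedures).** "Participant assignment will be concealed from both participants and evaluators". This covers knowledge of the assigned arm. It does not address knowledge of test results.

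No sentence in the article says that strength results are held back until the questionnaires have been completed.

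**The concern.** RDQ and Reflux-Qual (section 3.6.2) are answered by the participant, and they carry the trial's symptom and quality-of-life conclusions. MIP, S-index and spirometry do not measure reflux burden.

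The arms are meant to diverge on strength. Under section 3.7 the active load starts at 40% of MIP and can rise weekly, while the sham load stays at 7 cmH2O. The sample size in section 3.5 is planned on an effect size of 1.3 for MIP. A participant who is told that strength has risen may guess active training, and one who is told that it has not may guess sham. If that guess comes before the questionnaire, the answer may partly reflect expectation. Because the feedback would tend to differ by arm, so might the distortion. At stake is how far a difference in the self-reported secondary outcomes can be credited to the training.

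**Working it through.** The plan gives no figure of its own on this point, and its sample-size numbers do not bear on it. The check has three steps.

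**1. Does the ordering rule cover the questionnaires?** The rule directly follows a list that contains both strength tests and both questionnaires. Section 3.6 then applies the same opening phrase, all measurements, to the three time points, and Table 1 schedules both questionnaires at exactly those points. The literal reading therefore includes them. A narrower meaning, physical tests only, is possible but is not what the sentence says.

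**2. How often would a questionnaire come after a strength test?** Assumption: MIP, S-index, RDQ and Reflux-Qual are permuted with equal probability, giving 4! = 24 orders.

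- A given questionnaire precedes both strength tests when it is first of those three: probability 1/3. It therefore follows at least one strength test with probability 1 − 1/3 = 2/3 (16 of 24 orders).
- It follows MIP in particular with probability 1/2 (12 of 24).
- Both questionnaires precede both strength tests in 2! × 2! = 4 orders. At least one questionnaire therefore follows a strength test with probability 1 − 4/24 = 5/6 (20 of 24).

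These are probabilities of sequence. They become probabilities of knowing a result only if results are told during the visit.

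**3. When would a known result matter?** The article leaves the time of disclosure open, so each possibility is set out.

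| Results told | At T1 | At T2 | At T3 | Does order within a visit matter? |
|---|---|---|---|---|
| As each test is done | Baseline value only; no training gain to see | Gain may be known before a questionnaire | Gain at T2 already known | Yes, chiefly at T2 |
| At the end of each visit | Nothing known | Baseline known, gain not known | Gain at T2 known | No |
| After T3 only | Nothing known | Nothing known | Nothing known | No |

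The first two rows open a route to biased answers and the third closes it. All three fit the text of section 3.3.

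**The case against.** The strongest reply is that the article never says participants will be told strength results during follow-up. The item in section 3.3 belongs to a list of what is explained at recruitment. It does not mention MIP, T2 or T3, and the results meant could be the screening ones or those returned after the trial. The timing of such feedback is also a detail that a condensed article may leave to the full protocol. All of this stands. A reader might infer that participants will learn their strength gains mid-trial and that blinding is therefore broken, but the document does not support that.

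Other points also stand in part:

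- Random order applies equally to both arms, so by itself it creates no difference between them. It matters only together with disclosure during the visit.
- Participants may already sense whether their load is rising, so the extra unblinding from a disclosed result may be small.
- Section 3.6.1 acknowledges a learning effect on repeated measurement. Sham participants may therefore also see gains, which would weaken the clue.

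A reader might also be tempted to assume some shift in questionnaire scores and turn it into an inflated false-positive rate. The document gives no basis for any such shift, for how many participants it would affect, or for its absence in the sham arm. Any rate obtained that way would restate the assumption.

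What the reply does not remove is the ordering rule itself. It is stated, it covers all measurements, and nothing stated beside it keeps results from participants until they have answered the questionnaires.

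**Conclusion.** The point holds as a minor, cheaply removed weakness. As written, the article allows a participant in a sham-controlled trial to know a strength result before giving self-reported scores, either within a visit or from T2 to T3. It does not say that this will happen. The exposure is confined to the secondary outcomes RDQ and Reflux-Qual; MIP and S-index do not depend on questionnaire answers.

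The only size that can be given is the sequence probability: 2/3 for a given questionnaire and 5/6 for at least one of the two. It assumes that the ordering rule covers all four assessments with equal probability. The direction of any bias would plausibly favour the active arm, but its magnitude cannot be derived from the document.

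**What to change.** Two sentences would close both routes.

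- **Section 3.6:** state that RDQ and Reflux-Qual are completed first at every visit, before any breathing test, and that random order applies only to the physiological tests.
- **Section 3.3 and the participant information:** state that individual MIP and S-index results are given to participants only after their T3 visit. This concerns routine return of research results.

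The downside is that participants wait until T3 for their results. Sample size, intervention and analysis are unchanged. Section 5 says that no further modifications are allowed after ethics approval, so the team should establish with the committee whether these sentences count as clarification. If the full protocol already fixes the timing and order in this way, the article need only say so.

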### 3.5. Participants and Eligibility Criteria

Adults aged 18–70 years with a confirmed diagnosis of gastroesophageal reflux disease by a gastroenterologist are eligible to participate (inclusion criteria). Selection and initial assessment will be done by a physiotherapist [21,22]. Exclusion criteria include pregnancy, previous gastric or duodenal surgery, systemic connective tissue diseases, tuberculosis, and diagnosed mental disorders [23].

Participants’ characteristics: The sample will comprise participants of all genders, including both males and females with diagnosed GERD, from the Attica region. The minimum sample size was determined using the G*Power software (version 3.1.9.7), based on an effect size of 1.3 for MIP reported by Fonseca et al. (2014) [24]. Based on an effect size of 1.3, a statistical power of 0.80, and an α level of 0.05, the minimum required sample size was 22 participants. Accounting for a potential 15% dropout rate, the final minimum sample size was set at 25.

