### 3.7. Interventions

An informative session on diaphragmatic breathing with simulated inspiratory muscle exercise after randomization will be given to participants of both groups. This will enhance the role of physiotherapy, specifically the development of a trusting relationship between therapist and participant, increasing their self-confidence [39]. The long-term goals of managing the underlying disease and the health belief model will determine the structure of the session [40].

Intervention group: Participants allocated to the intervention group will follow a 12-week inspiratory muscle training program consisting of three 15 min sessions per week in the morning or afternoon 2 h after breakfast or lunch [41]. Training will be performed using an electronic inspiratory muscle trainer that provides a tapered flow of load resistance, initially at 40% of each participant’s MIP performing 30 breaths per session with 1 set of 30 repetitions [24,42]. Resistance will be progressively increased on a weekly basis at a rate of 10% of the initial maximal inspiratory pressure measurement if patients at the end of the week experience difficulty 3–4 on the Borg scale [43]. Otherwise, the resistance will remain the same. Resistance will also be maintained if the participants present persistent reflux symptoms.

Control group: Participants assigned to the control group will perform sham inspiratory muscle training using the same device with a constant minimal resistance 7 cmH_2_O [23].

A training diary will be kept for all participants that will include all information on the progression of training, missed sessions (along with the reason) and monitoring of their symptoms and medication.

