## 4. Analytical Approaches for Statistical Evaluation of the Data

Statistical analyses will be performed using the Statistical Package for the Social Sciences (SPSS, version 29; IBM Corp., Armonk, NY, USA). Prior to inferential analysis, data will be screened for completeness and distributional characteristics. The normality of continuous variables will be examined using the Shapiro–Wilk test. Descriptive statistics will be used to present and summarize participants’ characteristics.

To evaluate the reliability of repeated measurements across the assessment time points, intraclass correlation coefficients will be calculated for the primary outcome measures [44].

The primary analysis will focus on determining whether changes in outcome measures over time differ between the experimental groups. Repeated measures 2 × 3 ANOVA with Bonferroni correction will be used to examine interaction effects between group allocation (IMT vs. sham IMT) and time (T1, T2, T3) [44]. Additionally, we will evaluate differences between groups at each time point. Assumptions of homogeneity of variance will be assessed prior to model interpretation. Statistical significance will be set at an alpha level of 0.05 for all analyses.

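### Mandatory withdrawal from the study for missed sessions or worsening symptoms leaves a sample selected on adherence and on a secondary outcome, and the 15% dropout allowance is not tied to the rule

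*Protocol article*

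**What the plan says.** Section 3.3 makes withdrawal compulsory on either of two grounds: "failure to attend more than two scheduled treatment sessions or any deterioration in GERD symptoms will result in withdrawal from the study". It does not define deterioration by instrument or threshold, and it does not say that outcome assessment goes on afterwards.

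Section 3.7 sets the schedule as a "12-week inspiratory muscle training program consisting of three 15 min sessions per week". The same section keeps participants with persistent reflux symptoms in training at unchanged resistance. It also provides a diary of missed sessions with reasons, symptoms and medication.

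Sections 2 and 3.6.2 make GERD symptom severity, measured by the RDQ, a secondary outcome. Section 4 gives the main analysis over T1, T2 and T3: "Repeated measures 2 × 3 ANOVA with Bonferroni correction will be used to examine interaction effects".

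On numbers, section 3.5 works "based on an effect size of 1.3 for MIP", with "a statistical power of 0.80, and an α level of 0.05, the minimum required sample size was 22 participants". It then says: "Accounting for a potential 15% dropout rate, the final minimum sample size was set at 25". The abstract gives a different enrolment: "A total of thirty adults with a confirmed GERD diagnosis will be enrolled".

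**The concern.** Both grounds for withdrawal arise after randomisation. One is adherence. The other is a bad result on something that the trial sets out to measure. If training helps, more sham than trained participants worsen and leave, so the sham arm that remains looks better than the arm that was randomised. If training makes symptoms worse, the participants affected contribute no later outcome data. Either way, the symptom and quality-of-life comparisons are made among survivors of a selection rule.

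A repeated-measures ANOVA on three visits in its usual form uses only participants with all three, so it does nothing to undo the selection. A later analysis plan could name an all-randomised set, but it cannot recover T2 and T3 values that the protocol stopped collecting.

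There is also a planning question. A rule this strict may itself cause much of the attrition, yet the 15% allowance makes no reference to it.

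**Working it through.** **1. The plan's own sample size.** Inputs from section 3.5: d = 1.3, power 0.80, α 0.05. Two-sided testing and 1:1 allocation are assumed, as neither is stated there. The two-sample t-test (noncentral t) needs 10.34 per arm, so 11 per arm and 22 in total, with power 0.826. The stated 22 reproduces. Inflation for 15% loss: 22 / (1 − 0.15) = 25.9, so 26; the article has 25, a rounding difference of one.

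**2. Loss that still leaves 22.**
- From 25: (25 − 22) / 25 = 12%.
- From 30 (abstract): (30 − 22) / 30 = 26.7%.

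**3. What the attendance rule demands.** 12 × 3 = 36 sessions. Missing three or more triggers withdrawal, so at least 34 / 36 = 94.4% must be attended.

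**4. Loss from the attendance rule alone.** The article gives no attendance rate, so the per-session miss probability q is an assumption, as is independence of misses. Loss = P(X ≥ 3), with X ~ Binomial(36, q). At q = 5%, P(0) + P(1) + P(2) = 0.158 + 0.299 + 0.275 = 0.732, so the loss is 26.8%.

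| q | Loss | Enrolment needed to keep 22 |
|---|---|---|
| 2% | 3.5% | 23 |
| 3% | 9.3% | 25 |
| 4% | 17.3% | 27 |
| 5% | 26.8% | 31 |
| 10% | 71.2% | 77 |

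Loss reaches 15% at q = 3.7%, which is 36 × 0.037 = 1.3 missed sessions per person on average.

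**5. Adding symptom withdrawals.** With a symptom-withdrawal probability s (assumed, and independent of attendance), total loss = 1 − (1 − attendance loss)(1 − s).
- q = 3%: 18% for s = 10%, 27% for s = 20%.
- q = 5%: 34% for s = 10%, 41% for s = 20%.

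**6. Selection on symptoms.** Assume that symptom change is normal with SD 1, that negative values mean improvement, and that everyone above a cut-off c leaves. The mean of those who remain in an arm with mean μ is μ − φ(c − μ) / Φ(c − μ). For sham mean 0, IMT mean −0.8 and c = 0, the means are −0.798 and −1.168, so the contrast is −0.37.

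| Sham mean | True difference | Cut-off | Withdrawn, sham / IMT | Difference among those left |
|---|---|---|---|---|
| 0 | 0.8 | 0 | 50% / 21% | 0.37 |
| 0 | 0.8 | 0.5 | 31% / 10% | 0.48 |
| 0 | 0.8 | 1 | 16% / 4% | 0.59 |
| −0.5 | 0.5 | 0 | 31% / 16% | 0.28 |
| −0.5 | 0.8 | 0 | 31% / 10% | 0.48 |
| −0.5 | 0 | 0 | 31% / 31% | 0 |

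The last row shows that, when the rule is applied alike in both arms and there is no true difference, this mechanism creates none.

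**7. Primary outcomes.** The effect on MIP and S-index depends on how they relate to symptoms and attendance. The article gives nothing on that, so no figure is offered.

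**The case against.** A reader might infer that the rule makes the 15% allowance unrealistic. The document does not support that. It gives no attendance or worsening rate, and at a miss rate of 2% or 3% the attendance rule stays within 15%. The abstract's 30 also tolerates 26.7% loss, which is what the attendance rule costs at a miss rate of about 5%. Independence of misses matters too. If absences cluster within people (beta-binomial, assumed intraclass correlation 0.05 to 0.3), the loss at a 5% miss rate runs from 27% down to 18%. At 10% it runs from 57% down to 34%, so 71% is a high-end figure. At 3% clustering raises the loss, to between 11% and 15%. All of this stands.

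A reader might also infer that symptom harm would be hidden. That goes too far: the diary records symptoms and missed sessions, and section 6.3 provides contact after the trial about harm, so withdrawals for worsening could be counted by arm. What is lost is later outcome data.

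The symptom illustration equates the withdrawal trigger with a cut-off on the outcome itself, whereas section 3.3 does not tie deterioration to the RDQ. A looser link would weaken the selection. The table is an illustration and not an estimate.

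Analysis sets and missing-data methods are often left to an analysis plan, and their absence here is not the complaint. The complaint is a stated rule that ends participation. Section 5 says that no further modifications are allowed, but that is an administrative statement and does not make the rule sound.

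**Conclusion.** The point holds for the rule itself. Followed as written, section 3.3 leaves participants who attended at least 34 of 36 sessions and did not worsen, and the comparison between them is not the randomised one.

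Symptom and quality-of-life contrasts can be biased. Under normal symptom change with SD 1 and a true difference of 0.5 to 0.8 SD, the difference shrinks to roughly 0.28 to 0.59 SD. With no true difference and even application of the rule, there is no such bias. It would be tempting to say that the primary result is biased as well, but for MIP and S-index neither size nor direction can be derived from the document.

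The 15% allowance is unsupported and sensitive: it is used up at a miss rate of about 3.7% before any symptom withdrawal. It is not shown to be wrong.

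The rule should be changed before follow-up data are lost, because no later analysis can replace them.

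**What to change.** - In section 3.3 and the consent text, separate stopping of training from withdrawal from the study. When training stops is left to the clinical team. Every randomised participant is invited to T2 and T3 unless consent is withdrawn.
- In section 4, analyse all randomised participants in their allocated arm with a method that keeps incomplete cases, for example a likelihood-based mixed model on all available visits.
- Report participants who missed two or fewer sessions as a supportive per-protocol analysis, and report symptom deterioration by arm.
- State the basis of the 15% allowance, and reconcile the 25 in section 3.5 with the 30 in the abstract.
- Reconcile section 3.3, where deterioration ends participation, with section 3.7, where participants with persistent symptoms stay in training. The document should say how the two fit together; no clinical rule is proposed here.

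The cost is a short change to the text, an ethics amendment and a few more T2 and T3 visits. The effect estimate will then include participants who did not adhere.
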